## Abstract

**Background:**

Pediatric dental treatment is challenging in patients with early childhood caries. For clinician its difficult to manage child and provide good work at the same time. Its necessity to have the best equipments as well as materials. Nowadays, aesthetics play an important role in managing decayed teeth. Zirconia crown is better option but requires excessive preparation. As Bioflx is newly developed crown and has combined stainless steel and zirconia properties.

**Aim:**

To assess the clinical performance and child and parental satisfaction of Bioflex crowns compared to zirconia and stainless steel crowns.

**Methods:**

In this comparative study of Bioflx crowns with zirconia and stainless steel crowns, children aged three to seven years old will be selected, and 72 primary teeth requiring crowns will be randomly distributed into three groups, n = 24:
**Group I:** Preformed stainless steel crown, control;
**Group II:** Preformed Bioflex crown;
**Group III:** Preformed zirconia crown. Crowns will be evaluated for recurrent caries, plaque accumulation, restoration failure, gingival status opposing tooth wear, and clinicians and parental satisfaction at zero, three, six, and 12 months.

**Results:**

Bioflx crown will have better clinical as well as parental satisfaction among zirconia and stainless steel crowns.

**Conclusions:**

The Bioflx crown can be used as an alternative economical esthetic full-coronal restoration for primary teeth.

**Trial registration:**

CTRI registration number:
CTRI/2023/05/052256; Date of registration: May 03, 2023.

**Protocol version:**

Two; Date: April 22, 2023

## Introduction

### Background and rationale

In most preschoolers, early childhood caries pose a significant problem. If left untreated, they can lead to the degeneration of a child’s oral health.
^
1
^ Managing deciduous, deformed, decayed, or traumatized teeth with tooth-colored restoration is challenging in children because of their miniature tooth size, larger pulpal chamber, thin enamel, and decreased surface area for restoration, accompanied by specific behavior management problems in young pediatric patients. Aesthetic concern plays a vital role in modern dental practice. Understanding the child’s and parental aesthetic perception is necessary for good clinical practice.
^
2
^
^,^
^
3
^

An optimal anterior restoration should have better durability, ease of handling, be aesthetically acceptable, and be cost-effective. There have been many options for full coverage restoration of deciduous teeth, each with technical, functional, or aesthetic limitations.
^
3
^
^,^
^
4
^ The demand for beautiful smiles is increasing among children and adults. A child’s looks can affect their achievement in social acceptance, quality of life, and physical and psychological health. A variety of aesthetic solutions are available, including full-coverage crowns for deciduous anterior teeth, prefabricated primary zirconia crowns, and pre-veneered stainless-steel crowns. There is possibility of increasing in the occlusal vertical dimension after placing crown which may cause temporomandibular dysfunction. In children it is found that occlusal re-equilibration is attained after treatment.
^
5
^

The primary dentition should be preserved in a non-pathologic and healthy state for the child’s overall well-being. Pediatric dentists have to balance three priorities: the patient’s behavioral management, the conservation of the tooth structure, and the parents’ satisfaction.
^
6
^ Continually re-evaluating pediatric dental treatment modalities and techniques is necessary because the advancements in dental materials for children over the last few decades have led to constant improvement in dental materials suitable for children. Young patients may not necessarily benefit from a treatment approach that was acceptable in the past. There has been a concerted effort to bring various approaches for full coverage restorations in pediatric dental practice. Every technique and material has its merits and demerits. It is noted that there are numerous possibilities for treating carious teeth in young children, ranging from stainless steel crowns and their modifications to other aesthetic crowns like Bioflx and zirconium crowns, which are becoming more and more popular. Bioflx crowns are flexible, durable, and adaptable. They are available as aesthetic preformed pediatric crowns that offer properties of both stainless steel and zirconia crowns. There is a lack of literary evidence for assessment of the properties of Bioflx crowns and their effect on clinical outcomes and parental satisfaction compared to traditionally available options. Hence, this study plans to assess the clinical performance and child and parental satisfaction for Bioflx, zirconia, and stainless steel crowns in pediatric patients.

### Objectives

The objectives are as follows:
•To evaluate and compare the clinical performance of Bioflx, zirconia, and stainless steel crowns in primary dentition based on recurrent caries, gingival health, restoration failure, plaque accumulation, opposing tooth wear, and clinicians’ satisfaction at zero, three, six and 12 months follow up.•To assess the child and parental satisfaction of Bioflx, zirconia, and stainless steel crowns in primary dentition at zero, three, six, and 12 months.

## Methods

### Study design

A randomized controlled trial with a parallel group will be the research design for the study. Total 72 primary teeth requiring crowns will be randomly distributed in three groups of 24 each. The allocation will be carried out using computer-generated numbers. After obtaining written informed consent, the subjects will be enrolled, and teeth will be assigned randomly to the groups for receiving the intervention or conventional preformed crowns. The study adheres to the protocol following the Standard Protocol Items: Recommendations for Interventional Trials (SPIRIT) guidelines.
^
7
^ The allocation of participants and flow diagram for study participants is shown in
Figure 1.

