### Study setting and population

The present study will be conducted in the Department of Pediatric and Preventive Dentistry of Sharad Pawar Dental College and Hospital, Sawangi (Meghe), Wardha, Maharashtra, India.

In children with more than one tooth requiring a crown, the teeth will be allocated based on random sampling. We will be conducting single blinding in which participants will be blinded. Personal information about potential and enrolled participants will be collected and maintained in order to protect confidentiality before, during, and after the trial. The population of the study is young, healthy children. The research is approved by the institutional ethics committee of Datta Meghe Institute of Higher Education and Research (Deemed to be University) (ref. no: DMIHER (DU)/IEC/2023/565). (IEC) Institutional Ethical Committee Date of approval: February 6, 2023.

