### Eligibility criteria

Inclusion criteria
^
6
^ will be as follows:
•Children aged three to seven years old who are healthy and free of any systemic disease•Deciduous teeth indicated for crowns•Deciduous teeth having two-thirds of root structure left radiographically•Presence of one-third of crown shape

Exclusion criteria
^
6
^
•A pathological discrepancy of root resorption•Inflammation at the furcation area•The child having oral parafunctional habits•Deciduous teeth having not sufficient crown structure•Teeth with root caries

Evaluation criteria

The study will be clinically evaluated from the following criteria: crown retention, modified gingival index, plaque index, stain resistance, gingival marginal extension, occlusion, proximal contact, opposing tooth wear, and radiographic assessment.

Clinician’s Satisfaction Criteria will be as follows: surface gloss, roughness, stain resistance, aesthetic, anatomical form, crown fracture, recurrent caries. Parental satisfaction ratings of aesthetic characteristics and their impact of treatment on their children will be evaluated on the basis of size, shape, color and stain using five-point Likert’s scale.

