### Interventions

Total 72 primary teeth requiring crowns will be randomly distributed in three groups of 24 each. The allocation will be carried out using computer-generated numbers. After obtaining written informed consent, the subjects will be enrolled, and teeth will be assigned randomly to the groups for receiving the intervention or conventional preformed crowns.

Group 1: Preformed stainless steel crown: control group

(3M™ ESPE™)

The material for coronal build-up for this group is a preformed stainless-steel crown(the control group). An appropriate-sized preformed stainless-steel crown will be selected. Tooth preparation will be carried out with tapered bur (pyrax Dental Mani Diamond Burs TR-13C) to reduce occlusal surface up to 1 to 1.5 mm. The interproximal reduction will be made mesially and distally. The selected crown size will be checked and a trial fit will be done before cementation. It will require crimping pliers and the crown will be cemented using type 1 glass ionomer cement (GC Gold Label I/ Fuji I). The excess will be removed and proper occlusion will be checked.
^
8
^

Group 2: Preformed Bioflx crown

The Preformed Bioflx crown (
Kids-e-dental LLP [Limited Liability Partnership]) will be used in this group. A similar sized preformed crown will be selected. Tooth preparation will be carried out with a tapered diamond bur (pyrax Dental Mani Diamond Burs TR [Taper Round] -13C) for occlusal reduction by 1–1.5 mm, including the central groove. The proximal preparation will be around 0.5 mm to clear the contact area. Placement of the crown will be achieved by a snug fit followed by contouring using a How plier (GDC How Plier # Curved (3000/72).

Crown cementation will be carried out using a glass ionomer type I (GC Gold Label I/ Fuji I) and removal of excess cement using floss or explorer.

Group 3: Preformed zirconia crown

The material for crown restoration for this group is the preformed zirconia crown (Kids-e-dental LLP). A diamond bur will reduce the occlusal surface by 1.5–2 mm. Interproximally, contacts will be prepared with a tapered fissure bur. About 1–2 mm subgingival preparation will be performed. The selected crown will be placed and checked. The passive fit of the crown will be assessed and will be luted with dual cure resin cement (Prevest Fusion Ultra D/C / Dual Cure Resin). Consistent firm finger pressure will be applied during cementation. Crown placement will be assessed.
^
8
^

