### Data collection

The questionnaire for assessing child and parental satisfaction score consists of four main categories in satisfaction rating of esthetic characteristics.
^
1
^ These categories are size, shape, color, and stain. The response format will be a five-point Likert scale, ranging from not at all satisfied, with a score of 1, to very much satisfied, with a score of 5.

Another questionnaire scale based on parental ratings of the impact of treatment on their children
^
9
^ consists of five categories, including 1) The oral health of the child improved after crowns; 2) Parents concern about appearance before crowns; 3) The child avoided smiling before crowns; 4) Child smiling after crowns; 5) Crowns have improved the appearance of the child’s teeth. The response format will be a five-point Likert scale, ranging from not at all (score of 1) to very much (score of 5).
^
7
^
^,^
^
9
^

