## Discussion

The significance of conventional stainless-steel crowns in posterior full coronal restorations in early childhood caries cases are well acknowledged. They have been used for various purposes. To further improvise the longevity and need for better natural-looking restoration in primary teeth, this study plans to compare the Bioflx crown over conventional ones.

Stainless steel crowns have been used for decades and fulfill every aspect of a crown except the aesthetic purpose. As a result, tooth-coloured restorations like zirconia were introduced but they require subgingival preparation, which requires more time and is also not cost-effective for parents. The newly emerging Bioflx crown has super flexibility, is more adaptable, is easy to prepare, and is a faster technique for full coronal restorations in early childhood caries cases. Mathew
*et al*. (2020) conducted an
*in vivo* study in which bilateral pulp therapy was performed. Patients were divided into two groups of either zirconia or a stainless-steel crown. Patients were evaluated based on gingival inflammation, plaque accumulation opposing tooth wear, and parental satisfaction. They found no statistical difference between the clinical outcome success rates for zirconia and stainless-steel crowns, but less plaque accumulation was noted with zirconia in comparison to stainless-steel. With both the crown types, it seemed that parental satisfaction rates were high.
^
1
^

Gupta
*et al*. (2020) also conducted an
*in vivo* study to compare three tooth-coloured crowns and evaluate marginal integrity, surface texture, discoloration, anatomical form, and secondary caries in deciduous anterior teeth over a period of three, six, and nine months. Group I included resin strip crowns, Group II had zirconia crowns, followed by Group III, which had Luxa crowns. They found that the results were statistically non-significant for all parameters except the resin strip crowns, which showed secondary caries and irregular marginal integrity. The zirconia crown showed the best results among the three crowns, followed by the Luxa crown.
^
6
^

Olegário

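### Eligible tooth position is left open and the text points both ways; if anterior and posterior teeth are both enrolled, stratify the allocation by position and adjust for it, since chance imbalance at 24 per arm can distort (not overwhelm) the satisfaction comparison

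*Protocol article*

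**What the plan says.** Allocation (Protocol article, Study design): "Total 72 primary teeth requiring crowns will be randomly distributed in three groups of 24 each", and "The allocation will be carried out using computer-generated numbers". For children with several affected teeth, Study setting and population adds: "In children with more than one tooth requiring a crown, the teeth will be allocated based on random sampling". No blocking or stratification factor is named in these sections, under Participant allocation/randomisation or under Interventions.

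Tooth position:
- **Eligibility criteria:** "Deciduous teeth indicated for crowns". The further conditions concern root and crown structure and pathology, not position.
- **Background and rationale (anterior):** "An optimal anterior restoration should have better durability, ease of handling, be aesthetically acceptable, and be cost-effective".
- **Discussion (posterior):** "The significance of conventional stainless-steel crowns in posterior full coronal restorations in early childhood caries cases are well acknowledged".
- **Interventions (posterior-type anatomy):** all three groups have an occlusal surface reduced; for Bioflx the text reads "for occlusal reduction by 1–1.5 mm, including the central groove".

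Outcome and analysis: the satisfaction questionnaire rates aesthetic characteristics ("These categories are size, shape, color, and stain"), and a second one asks parents about smiling and appearance. The Data analysis section compares the three groups by ANOVA or Kruskal-Wallis and names no covariate.

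**The concern.** A reader cannot tell whether front teeth are in the trial. If they are, a metal crown on a visible front tooth and one on a molar may well be rated differently for colour and appearance. Opposing tooth wear, proximal contact and occlusion may also depend on position. With 24 teeth per arm and nothing in the stated scheme to balance position, one arm may by chance hold noticeably more anterior teeth than another. The unadjusted comparison would then carry part of the position effect inside the crown effect, and variance that position could explain would stay in the error term.

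**Working it through.** **1. The plan's own figures.** Sample size assumes satisfaction of about 99.9% against 53.3%, two-sided alpha 1% (z = 2.576) and power 90% (z = 1.28). The design difference is 99.999 − 53.333 = 46.666 points. The pooled-variance formula reproduces 22 per group:

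(2.576 × √(2 × 0.766 × 0.234) + 1.28 × √(0.999 × 0.001 + 0.533 × 0.467))² / 0.466² = (1.542 + 0.640)² / 0.2172 = 21.9, so 22.

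Adding 2 for dropout gives 24. (The unpooled formula that is printed gives 17.1, so 18; that is a separate matter and is not used below.) The standard error of the difference at 24 per arm is √((0.000999 + 0.248911) / 24) = 0.102, or 10.2 points.

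**2. Size of chance imbalance.** The anterior share is an assumption. With K anterior teeth among 72 allocated to fixed arms of 24, π = K/72, and the SD of the difference in anterior share between two arms is √((72/71) × π(1 − π) × 2/24). For K = 36: √(1.0141 × 0.25 × 0.0833) = 0.145. The probabilities come from 400,000 simulated allocations. A gap of at least 20 points means at least 5 teeth (5/24 = 20.8 points).

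| Anterior share (K) | SD of gap | Gap ≥ 20, given pair | Gap ≥ 20, some pair | 95th percentile of gap, given pair |
|---|---|---|---|---|
| 10% (7) | 8.6 | 2.5% | 6% | 4/24 = 16.7 |
| 20% (14) | 11.5 | 10% | 22% | 5/24 = 20.8 |
| 30% (22) | 13.4 | 16% | 33% | 6/24 = 25.0 |
| 50% (36) | 14.5 | 20% | 42% | 7/24 = 29.2 |

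**3. Effect on the satisfaction difference.** Shift = gap × position effect, taking the position effect as additive. The documents give no position effect, so 20, 30 and 46.7 points are assumed; the last equals the whole design difference. At the 95th percentile of the gap:

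| Anterior share | Effect 20 | Effect 30 | Effect 46.7 |
|---|---|---|---|
| 10% | 3.3 | 5.0 | 7.8 |
| 20% | 4.2 | 6.3 | 9.7 |
| 30% | 5.0 | 7.5 | 11.7 |
| 50% | 5.8 | 8.8 | 13.6 |

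The largest entry is 13.6 / 10.2 = 1.3 standard errors, or 13.6 / 46.7 = 29% of the design difference. Cancelling the design difference with a 46.7-point position effect would need a 100-point gap.

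**4. Error rate and power.** Simulated two-arm comparison, 24 per arm, normal outcome, 30% anterior, alpha 1%, 6,000 runs per setting. With no treatment effect, the unadjusted test under unstratified allocation rejected in 0.98% to 1.08% of runs. Power for a treatment effect of 1 SD:

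| Scheme | Position effect 0.5 SD | Position effect 1 SD |
|---|---|---|
| Unstratified, unadjusted | 75% | 68% |
| Unstratified, adjusted | 76% | 77% |
| Stratified, unadjusted | 76% | 69% |
| Stratified, adjusted | 78% | 78% |

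Most of the gain comes from adjustment; stratifying without adjusting leaves most of it unused.

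**5. After stratification.** With blocks of 3, an unfinished block leaves the arms at most 1 anterior tooth apart: 1/24 × 46.7 = 1.9 points at the largest assumed effect. With a block of 6 it is at most 2 teeth: 2/24 × 46.7 = 3.9 points.

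**The case against.** **The effect is modest on the trial's own terms.** A 20-point gap with a 46.7-point position effect shifts the estimate by 0.20 × 46.7 = 9.3 points, below one standard error. Randomisation already covers chance imbalance in the error rate. This stands. A reader might infer that imbalance could swamp the comparison or invalidate the test; neither follows from the figures.

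**Position may not matter much.** No document gives an effect of position on satisfaction. A reader might infer that position is the dominant determinant of the rating; nothing in the text supports a ranking. What remains is that it plausibly matters for ratings of colour and appearance.

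**The mix may be small.** Occlusal reduction in every group, a central groove for Bioflx and an exclusion for furcation inflammation all suggest molars. Against that, the eligibility list cites the study that the Discussion describes as a comparison of crowns in anterior teeth, and the rationale is anterior. The ambiguity is real, and the 50% row is the worst case, not an expectation.

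**Arm sizes.** A reader might take computer-generated numbers to mean unrestricted randomisation with unequal arms. The article states 24 per group, so that reading is unsupported.

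**A condensed article is silent on many details.** The flow diagram and extended data are not at hand, and a fuller protocol may name a stratification factor. So the silence itself is not the fault. What stands is the conflict in the text over which teeth are meant, and that a better method than the one stated is available at little cost.

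**Conclusion.** The point holds as a design improvement, not as a threat to validity. Eligibility leaves position open, the surrounding text points both ways, and nothing stated balances or adjusts for it. If both positions are enrolled in substantial numbers (20% to 50% anterior), a gap of 20 points or more in some pair of arms has a 22% to 42% chance; at 10% anterior it is 6%. The likely upper range of the shift in the satisfaction difference is 3 to 14 points.

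That can distort the comparison with stainless steel but is small beside the assumed 46.7 points. It matters most for Bioflx against zirconia, for which the protocol gives no expected difference and its Conclusions anticipate similar results, so a shift of this size could rival the true effect. One limit applies there: if both crowns came near the 99.9% assumed for the experimental group, a yes/no satisfaction outcome would leave little room for a position effect.

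The figures rest on assumed anterior shares, assumed additive position effects and treating the 72 teeth as separate units.

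**What to change.** 1. Reconcile the Background, Eligibility criteria, Interventions and Discussion on tooth position, and state in Eligibility which positions are included.
2. If both remain, generate a permuted-block list (for example blocks of 3 and 6) separately for anterior and posterior teeth, using the position of the randomised tooth.
3. Include position in the analysis. Plain Kruskal-Wallis takes no covariate, so use a linear or ordinal model with position as a factor, or a rank test stratified by position.
4. If only molars are included, say so; stratification by position is then unnecessary.

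The cost is a second allocation list and a slightly more complex model. Unfinished blocks may also leave arm totals a tooth or two away from 24. The sample size stays at 22 + 2 = 24 per group. The article says that the study has not started, so the change can be made before enrolment.

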**Figure 1. f1:**
[figure not shown]
Flow diagram of study participants.

### Study setting and population

The present study will be conducted in the Department of Pediatric and Preventive Dentistry of Sharad Pawar Dental College and Hospital, Sawangi (Meghe), Wardha, Maharashtra, India.

In children with more than one tooth requiring a crown, the teeth will be allocated based on random sampling. We will be conducting single blinding in which participants will be blinded. Personal information about potential and enrolled participants will be collected and maintained in order to protect confidentiality before, during, and after the trial. The population of the study is young, healthy children. The research is approved by the institutional ethics committee of Datta Meghe Institute of Higher Education and Research (Deemed to be University) (ref. no: DMIHER (DU)/IEC/2023/565). (IEC) Institutional Ethical Committee Date of approval: February 6, 2023.

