### Sample size

A sample size of children aged three- to seven-years-old will be selected and 72 primary teeth requiring crowns will be randomly distributed in three groups of 24, as follows:

$$N=\frac{{\left(Z_{\left(\alpha /2\right)}+Z_{\beta }\right)}^{2}\left(P_{1}\left(1-P_{1}\right)+P_{2}\left(1-P_{2}\right)\right)}{{\left(P_{2}-P_{1}\right)}^{2}}$$
(1)

$$Z_{\alpha /2}=\text{at 99\% (CI)}=2.576$$

Represents the desired level of statistical significance

$Z_{\beta }=1.28$
: Represents the desired power = 1.28 for 90%

*N* = Minimum samples required for each group

Where,

*P*
_1_ = Estimated proportion of study outcome (Child satisfaction % Experimental group) = 99.99% (Approximate to 100%)
(1)
^
1
^

*P*
_2_ = Estimated proportion of study outcome (Child satisfaction % Control group) = 53.33%
^
1
^

At a level of significance at 1% and power 90%

The minimum sample size required:

$$N={\left(2.576+1.28\right)}^{2}\;{\left(0.999\right)}^{*}\;\left(1-0.999\right)+{\left(0.533\right)}^{*}\;\left(1-0.533\right)/0.466=22\;\mathrm{per}\;\text{group}$$

Considering 10% dropout=2

Samples required22+2=24each

$$\text{Total samples required for three groups}=3^{*}N=72\;\text{total}$$

Mathew
*et al.,* showed the difference between the two proportions of child satisfaction (%) as the primary variable
(1)
^
1
^

P1(for the experimental group) = 100% (considered as 99.999% approx to 100%) and for the control group (53.333%). We considered a clinically significant margin of difference at 46.666%. Also, we considered the assumption for statistical significance, the highest statistical significance level of 1% alpha value with power (1-beta) at 90%.

We use the test statistics of two independent proportion sample size calculations with the given formula samples for taking the minimum samples required in each group.

Calculated with 22 samples required in each group, adding 10% of dropout = 2. A total of 22 + 2 = 24 samples are required in each group, with a sample size of 72 children distributed in three groups.

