### Participant allocation/randomisation

The participants will be allocated based on the inclusion criteria. They will be randomized to preformed Bioflx crown and preformed zirconia crown as the intervention group or preformed stainless steel crown as the control group by computer-generated numbers. The research co-investigator will carry out data collection, data entry, and data analysis and will be blinded to group allocation.

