### Outcome measures

Preformed esthetic crowns and preformed stainless steel crown outcomes will be assessed by the research co-investigator at different time intervals of zero, three months, six months, and 12 months follow-up based on clinical performance, and child and parental satisfaction based on three evaluation criteria, which include clinical, clinicians’ and parental satisfaction. The child and parental satisfaction score will be measured using a questionnaire-based five-point rating Likert’s scale.
^
1
^ Outcome will be evaluated based on durability, flexibility, self adaptability. Bioflx crowns will be a smart option for pediatric tooth-coloured crowns.

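### The two blinding statements disagree, and neither can hold for stainless steel against the tooth-coloured crowns; giving the analysis to the outcome assessor also loses the one blind available

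*Protocol article*

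**What the plan says.** Two places in the protocol article say who is blinded:

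- Study setting and population: "We will be conducting single blinding in which participants will be blinded".
- Participant allocation/randomisation: "The research co-investigator will carry out data collection, data entry, and data analysis and will be blinded to group allocation".

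Under Outcome measures, the same role is the assessor: "outcomes will be assessed by the research co-investigator at different time intervals of zero, three months, six months, and 12 months follow-up".

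The arms differ in appearance by the article's own account. The Discussion says of the control: "Stainless steel crowns have been used for decades and fulfill every aspect of a crown except the aesthetic purpose". It describes zirconia as tooth-coloured, and Outcome measures says the same of Bioflx: "Bioflx crowns will be a smart option for pediatric tooth-coloured crowns".

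The ratings depend on appearance. For the child and parental satisfaction questionnaire, Data collection says: "These categories are size, shape, color, and stain". Under Eligibility criteria, the clinician's criteria are "surface gloss, roughness, stain resistance, aesthetic, anatomical form, crown fracture, recurrent caries".

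The Sample size section rests on child satisfaction. It cites a study that "showed the difference between the two proportions of child satisfaction (%) as the primary variable" and takes 100% for the experimental group against 53.33% for control.

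**The concern.** Blinding is a stated property of the design, and readers will carry it into their appraisal of the results. Here it is stated twice, for different people, and in both places the person named must look at the crown to produce the outcome. A report that repeats the label would describe the comparisons with stainless steel as blinded when they are open. Those comparisons include the self-rated outcome that sets the sample size.

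The second problem is avoidable. Rating a visible crown cannot be masked against metal, but analysis can be separated from examination. The plan gives both to one person.

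**Working it through.** No arithmetic decides this point, and no design figure (24 teeth per group, 72 in total) changes with it. The check sets the statements side by side.

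**1. Who is blinded?** The first statement is a single blind with participants as the blinded party. The second adds a blinded data collector and analyst. If the second is true, the trial is more than single-blind. If the first is complete, the second is wrong. They need to be reconciled whatever the crowns look like.

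**2. Can the participant blind hold?** The arms are one metal crown and two tooth-coloured crowns, which give three pairs:

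| Pair | Appearance | Can the child be unaware of type? |
|---|---|---|
| Stainless steel v Bioflx | metal v tooth-coloured | No |
| Stainless steel v zirconia | metal v tooth-coloured | No |
| Bioflx v zirconia | both tooth-coloured | Possibly |

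A child asked to score colour has to look at the crown, and the metal is then apparent. All 24 stainless steel crowns are identifiable in this way. Recruitment and consent also calls for children with more than one tooth needing a crown, and Study setting and population allocates such teeth at random. One child may therefore carry a metal and a tooth-coloured crown at the same time.

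**3. Can the assessor blind hold?** Outcome measures has the research co-investigator assess at all four time points. Surface gloss, aesthetic and anatomical form are judged by inspecting the crown. An examiner who does this knows which crowns are metal. No masking step is described.

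**4. Can the analyst blind hold?** Analysis is assigned to the same co-investigator. Someone who has examined the teeth and entered the records has already seen which are metal. A separate analyst working from coded arms could be blinded, but the text assigns the task otherwise.

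**5. Which outcomes are exposed?** The four satisfaction items are ratings of the crown. Of the five parental impact items, two concern the period before crowns (concern about appearance, and avoidance of smiling), so 5 − 2 = 3 concern the result of treatment. Of the seven clinician items, crown fracture and recurrent caries are closer to clinical events, which leaves 7 − 2 = 5 that are mainly judgements of surface and form. The sample size rests on child satisfaction, with a margin of 46.666 percentage points between experimental and control groups. The outcome it relies on is therefore among those rated with the metal in view.

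**The case against.** The strongest reply is that open rating against metal is unavoidable, and that for colour it is not even a fault. Seeing the crown is how an aesthetic effect arises, so a lower colour score for a metal crown is largely the outcome itself. This stands. What remains is expectation or novelty influencing the scores, which the document gives no means of sizing. The defect is the claim of a blind that the design cannot have, together with an analysis that is needlessly unblinded.

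Several stronger readings are tempting, but the text does not support them:

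- **That parents are said to be blinded.** Only participants are named, and the article elsewhere distinguishes participants from their parents.
- **That no blinding is possible anywhere.** A child or parent may not be able to tell Bioflx from zirconia, and that comparison is part of the aim.
- **That every rated item is subjective.** The before-crown impact items, crown fracture and recurrent caries do not fit that description.
- **That the investigators simply expect Bioflx to win.** The abstract's Results paragraph says so, but the Conclusions section expects similar results in all groups.
- **That the data pass through one pair of hands unchecked.** Data entry and storage has the principal investigator review entries and a co-investigator spot-check sheets. This controls errors, though it does not restore blinding.
- **That the examiner administers the questionnaires.** The article does not say how they are given.

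**Conclusion.** The point holds for stainless steel against Bioflx and against zirconia, two of the three pairwise comparisons. The two blinding statements conflict, and neither is attainable there for the child or for the co-investigator who assesses outcomes. Because that assessor is also the analyst, the analysis is not blinded as planned.

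A reader might infer that the article claims its subjective outcomes are protected from bias. It does not say so. It makes two short blinding statements and draws no such conclusion from them. Nor does an open comparison with metal make the trial invalid.

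The conclusion assumes only that a metal crown can be told from a tooth-coloured one by anyone who looks at it, which the article's own account of the crowns supports. The size of any resulting bias cannot be derived from the document. A fuller protocol could add procedures, but it could not make these two statements true for the comparisons with metal.

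**What to change.** Study status says the trial has not begun, so all of this can be done before enrolment:

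1. Replace the statements under Study setting and population and Participant allocation/randomisation with a single account of who is blinded.
2. State in it that children, parents and the clinical examiner are not blinded for comparisons with stainless steel. Add that, at most, the child and parent may be unaware of crown type between Bioflx and zirconia.
3. Code the arms A/B/C in the analysis dataset and have the analysis run by an existing investigator who does not examine the children. Colour scores may still hint at the metal arm, so the coding is a safeguard and not a guarantee.
4. Report satisfaction and aesthetic ratings against stainless steel as unblinded.

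The cost is protocol wording and one task moved between existing investigators. Sample size, visits and treatment are unchanged. The small downside is that the trial can no longer be labelled simply single-blind.
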